## Background

Plantar fasciopathy is a common cause of foot pain in both primary and secondary care. Plantar fasciopathy was formerly known as plantar fasciitis in literature. It typically affects middle aged or older women (40–60 years), with being overweight as a risk factor [1–3]. Besides this, plantar fasciopathy is also commonly seen in highly physically active people; plantar fasciopathy accounts for 8–10 % of all running related injuries [4]. Plantar fasciopathy accounts for approximately 11 to 15 % of all foot symptoms requiring professional care among adults and it has been estimated that a general practitioner (GP), with an average size practice, diagnoses around eight new patients each year [5, 6].

The etiology of plantar fasciopathy is poorly understood and is probably multifactorial [7, 8]. Histopathology studies have indicated that fasciopathy of the plantar fascia might be a possible cause of pain [9, 10]. Repetitive microtrauma and inflammation have been suggested as possible etiologic mechanisms, however these conclusions are mostly based on clinical experience and there is little evidence from research [11–13].

Plantar fasciopathy is characterized by pain over the anteromedial aspect of the inferior heel and the pain tends to increase after periods of inactivity or during weight bearing activities. The diagnosis can be made primarily based on symptoms and physical examination [7]. Patients often report low quality of life and reduced participation as their heel pain prevents them from performing simple every day activities [14, 15]. The clinical course of plantar fasciopathy is considered favorable as 80 % of patients will have a complete resolution of symptoms within 12 months [7]. Despite the favorable clinical course on the long term, many patients do expect and hope for short term pain relief and often multiple treatments are applied during the course of their complaints [7, 16].

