### Patient selection

Patients with plantar fasciopathy, characterized as pain at the medial hind foot, presenting themselves to a GP or sports physician, aged between 18 and 65 years and a minimal pain duration of 2 weeks are eligible for participation.

Participants will be excluded if they have recurrent complaints of plantar fasciopathy for more than 2 years, complaints caused by trauma, earlier treatment for plantar fasciopathy by a podiatrist or treatment with orthotics, suspected (by the GP or sports physician) (osteo)arthritis in the subtalar or talonavicular joint, suspected tarsal tunnel syndrome, suspected stress fractures, infections or tumors in the painful foot or presence of systemic diseases (such as Bechterew’s disease, psoriasis or multiple sclerosis). Patients who have no sufficient understanding of the Dutch language will also be excluded, since they will not be able to complete the questionnaires.

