### Sample size

Based on the RCT of Landorf et al. (2006) [18] –pain score 63.4 (SD 21.5), with a difference in pain score of 10.5 (on a scale of 0–100) – it is estimated that with a power of 80 % and an alpha of 0.05 (two-sided), it is possible to detect an effect size of 0.5 with 10.5 points difference on the pain score between patients with a placebo insole and custom made insole with 63 patients in each study group. In addition, a larger difference is expected between the custom made insole group and the usual care group. With a 12-point difference and identical means and SDs, a total of 44 patients are needed per group. A Bonferroni correction will be performed for the secondary comparisons to the usual care group. Taking a loss to follow-up of 10 % into account, a total of 185 patients with plantar fasciopathy (69 in custom made group, 69 in placebo group and 47 in usual care group) will be included in the trial.

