### Data analysis

Differences between the intervention groups will be analyzed following the intention-to-treat principle. Linear regression techniques for repeated measurements will be used to compare pain severity between the intervention group and control groups, which take the correlation of multiple measurements within one patient into account. A Bonferroni correction will be performed for the secondary comparisons to the usual care group. The analysis will be adjusted for potential confounders (at least including age, gender, BMI and activity level).

Recovery, pain scores and function will be analyzed using regression techniques for repeated measures using generalized mixed models.

Mean direct, indirect and total costs will be estimated and compared between the three study groups. Because costs will not be normally distributed, 95 % confidence intervals for the differences in mean costs will be obtained by bias corrected and accelerated bootstrapping (2000 replications). Differences in costs and differences in recovery will be included in a cost-effectiveness ratio, which estimates the additional costs to completely recover one patient.

Confidence intervals for the cost-effectiveness ratio will be calculated with bootstrapping, using the bias-corrected percentile method with 5000 replications. An incremental cost-effectiveness ratio will be estimated of the incremental costs to recover one patient. Uncertainty of this ratio will be evaluated by presenting a cost-effectiveness plane and sensitivity analyses will be performed to check the robustness of the results. An acceptability curve will also be presented.

Pre-defined subgroup analysis will be performed in patients with a long (>12 months) and short (<12 months) duration of the complaints at baseline, in patients with a low, moderate or high total activity score derived from the SQUASH questionnaire (in tertiles), in patients recruited in general practice and by sports physicians and in patients where the podiatrist agrees with the indication for orthotic insoles and in patients where the podiatrist does not.

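### Effect modification by symptom duration and SQUASH activity is pre-defined only in categories; adding continuous interaction terms would be a cheap, low-priority gain in power

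*Protocol article*

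**What the plan says.** The last paragraph of Data analysis in the protocol article lists four pre-defined subgroup analyses. Two use a modifier that is, or may be, measured on a numerical scale:

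- Duration, split into "patients with a long (>12 months) and short (<12 months) duration of the complaints at baseline".
- Activity, analysed "in patients with a low, moderate or high total activity score derived from the SQUASH questionnaire (in tertiles".

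The other two (recruitment setting, and the podiatrist's agreement with the indication) are categorical by nature and are not at issue here.

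The paragraph gives no reason for either cut, names no continuous alternative, and does not say whether the tertiles would be compared with a 2-df test or a trend. Its wording would also allow separate analyses within each category. Baseline measurement lists duration of pain as an item without its response format. The SQUASH total must be numerical, since it is to be cut at sample tertiles. The Sample size section covers only the main comparisons.

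**The concern.** These analyses ask whether the insole effect depends on how long the patient has had symptoms or how active the patient is. The authors consider activity a plausible modifier: Randomization procedure says that BMI and activity level might influence treatment response. Grouping a numerical modifier treats all patients within a group as alike. If the effect changes gradually, that discards information, and a three-group comparison also spends two degrees of freedom where a slope spends one.

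At stake is the trial's ability to show who benefits more or less, using data it largely already plans to collect.

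**Working it through.** **Inputs from the Sample size section.** "an alpha of 0.05 (two-sided"; "with a power of 80" %; "pain score 63.4 (SD 21.5"; "an effect size of 0.5 with 10.5 points difference on the pain score"; 63 analysable patients per insole arm, so N = 126 in the custom-placebo pair.

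**The plan's own figure.** n per arm = 2(1.960 + 0.842)² / 0.5² = 62.8, rounded up to 63. This agrees with the plan. (The unrounded 10.5/21.5 = 0.488 would give 66.) The plan states no power for the subgroup analyses, so there is nothing to reproduce there.

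**Assumptions not in the article.** The modifier is normal (for duration, after a log transform). Modification is linear, with gradient g, in outcome SDs of treatment effect per SD of the modifier. The share with more than 12 months ranges from 10% to 50%. The outcome is treated as a single week-12 value.

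**Formula.** The interaction F-test has noncentrality λ = (N/4) × g² × R². R² is the share of modifier variance that the coding keeps:

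- continuous: R² = 1
- tertiles of a normal variable: R² = 0.793
- two-way cut with a share p above it: R² = φ(c)² / [p(1 − p)], where c is the cut-point. For p = 20%, 0.280² / 0.16 = 0.490.

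For g = 0.5, λ = 31.5 × 0.25 = 7.875 on the continuous scale. For g = 0.3, λ = 31.5 × 0.09 = 2.835. Multiply by R² for the other rows.

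| Coding | R² | Power, g = 0.5 | Power, g = 0.3 |
|---|---|---|---|
| Continuous, 1 df | 1 | 79.5% | 38.6% |
| Tertiles, 2 df | 0.793 | 59.1% | 24.4% |
| Tertiles, 1-df trend | 0.793 | 69.8% | 31.9% |
| Cut, 50% above 12 months | 0.637 | 60.3% | 26.6% |
| Cut, 30% above | 0.576 | 56.1% | 24.5% |
| Cut, 20% above | 0.490 | 49.6% | 21.5% |
| Cut, 10% above | 0.342 | 37.0% | 16.5% |

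A simulation with g ≈ 0.50 (3,000 runs) gave 78% continuous, 58% tertiles on 2 df, 69% trend, 59% median cut and 45% for a 20% cut.

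**Equivalent sample size.** With g set at 0.503, so that the continuous test has exactly 80%, the pair would need about 195 patients to regain 80% with tertiles (2 df). With the cut it would need 197, 218, 256 or 365 if 50%, 30%, 20% or 10% are above 12 months.

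**Sensitivity to the assumptions.** For a uniform modifier, tertiles keep 89% and a median cut 75%. If modification is linear in a strongly skewed raw score (log-normal, SD 1 on the log scale), tertiles keep 39%. If the truth is a step exactly at a tertile boundary, tertiles keep everything and a linear term keeps about 59%.

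**If each category is analysed separately.** A tertile has 63/3 = 21 patients per arm and about 35% power for d = 0.5 (t-test).

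**The case against.** The case against giving this much weight is strong in several respects.

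- **The gradient is large.** At g = 0.5, with an average effect of 0.5 SD, the insole effect would be zero at 1 SD below the mean of the modifier and doubled at 1 SD above. Nothing in the article supports a gradient as large as the whole planned effect. At 0.3 the continuous test also misses more often than it detects, mainly because of the sample size. This stands.
- **The long-duration group need not be small.** A reader might infer that it will be, because the Background says that 80 % of "patients will have a complete resolution of symptoms within 12 months" and Patient selection excludes "recurrent complaints of plantar fasciopathy for more than 2 years". The first is a statement about clinical course, not about the duration of symptoms among those who consult and enrol. The second concerns recurrent complaints, and does not clearly cap continuous ones. The share above 12 months is unknown, hence the range.
- **Duration may not be recorded numerically.** The article does not say. If it is collected in bands, a log-duration term is not available as described.
- **The categories do not waste most of the information.** Tertiles of a normal modifier lose about 21%. The cut loses more than half only if about 20% or fewer are above 12 months.
- **A threshold effect would favour the groups.** A spline check at this sample size would itself have limited power.
- **The article is condensed.** An analysis plan not shown could add continuous terms. Readable clinical groups are also a common choice.

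These points limit size and priority. They leave the direction intact for a gradual effect: the article fixes the groups as the pre-defined analysis and names nothing beside them.

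**Conclusion.** The point holds as a low-priority improvement. Under roughly linear modification of about 0.5 SD per SD, the planned categories reduce power from about 80% to about 59% for SQUASH tertiles (70% with a trend test), and to between 60% and 37% for the duration cut. Under a gradient of 0.3 the drop is from about 39% to 24%, and to roughly 16% to 27%. These figures rest on an assumed modifier distribution, linearity and an assumed share above 12 months.

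A reader might go further and infer that a true gradient would be found with continuous terms, or that the report will declare no difference. The article supports neither: at moderate gradients both approaches are underpowered, and it says nothing on how a null subgroup result would be worded. The primary comparison, its sample size and its conclusion are unaffected.

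**What to change.** In the subgroup paragraph, make the test of effect modification a treatment-by-SQUASH-total-score term and, if duration is recorded numerically, a treatment-by-(log)-duration term, estimated at week 12 in the repeated-measures model. Check non-linearity with a simple spline. Keep the 12-month and tertile groups for display, and state that the subgroup analyses are not expected to be conclusive at this sample size.

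The cost is a sentence or two of analysis text and no new patients. No new data are needed for SQUASH, nor for duration if it is already numerical. The price is a linearity assumption, and less sensitivity than the groups would have if the true effect is a step at one of the cut-points.

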## Discussion

In order to explore the effectiveness of custom-made insoles, we will compare the insole to a placebo insole. One earlier study found similar effects on pain and function at both short and long-term follow-up between placebo insoles and custom made podiatric insoles [18]. Since both groups showed improvement during follow-up, the improvements seen in pain reduction might be caused by either a real placebo effect or the natural course of the condition. Therefore, we will also compare custom made insoles with usual care.

It has also been acknowledged that the placebo effect plays a role in clinical trials using orthotic devices and that the development of a placebo intervention in these trials is a difficult task [39]. For the current study purpose we will design a custom placebo insole for each foot separately. As a consequence each subject in the placebo insole group will be provided with an insole that gives as little support as possible. The material and the features of the custom-made insole cannot be identical to the placebo insole, since this would interfere with its function. However, we will make the placebo insole look as similar to the orthotic insole as possible (in shape), by producing placebo insoles tailored for each patient. By doing this, the placebo insoles will have a 3D effect (but lower than the custom made insole), without expecting therapeutic effects. By making both type of insoles look as similar as possible, we hope to achieve successful blinding of patients for the type of treatment received. We will assess success of blinding of patients by means of a single question in the 26 week questionnaire.

We expect to find a larger difference between the custom made insole group and the usual care group, compared to the custom made and placebo insole groups, since patients allocated to the usual care group are likely to have a different attitude towards their treatment. It is worthwhile to study these differences since this provides information on the treatment with custom made podiatric insoles compared to other strategies used in daily practice and on the possible placebo effect involved with treatment with insoles. This knowledge will improve the insight into the treatment of plantar fasciopathy as it is currently given in clinical practice.

We will include patients from both general practice and sport medicine clinics. Previous studies have suggested possible subgroups of patients, which might be represented by the two different recruitment settings. For example, patients recruited in general practice are more likely to be middle-aged with perhaps higher mean BMI’s, whereas patients recruited by sports physicians are probably more physically active compared to those in general practice. By performing a stratified randomization for type of referral we will be able to analyze the possible difference in effectiveness of insoles in subgroup analysis.

Our sample size calculation is based on the data from Landorf et al. [18] This trial is to tour knowledge the only trial that has compared a custom made insole to a sham insole. The pain score in this trial was derived from the Foot Health Status Questionnaire, which is a pain score with a scale from 0 to 100. The primary outcome of the present study is pain severity measured on a 0–10 point NRS-scale. In order to determine our sample size, we have rescaled the pain severity outcomes for application on the 0–10 NRS.

The strength of this study is that we will perform a trial in which we will compare custom made insoles, a preferred treatment in patients with plantar fasciopathy, to a placebo treatment and usual care. The results will contribute to clinical decision making in primary health care when it comes to plantar fasciopathy and will additionally provide information on the cost-effectiveness of podiatric care including orthotic insoles.
